### Allocation and sequence generation

The allocation sequence will be generated by center computer. When the participants voluntarily join this study with informed consents, the practitioner will open the webite (http://iwrs.tice.com.cn/) and evaluate the inclusion and exclusion criteria. If they are accorded with the inclusion criteria, the computer will generate a random number and show which group the participant should be in, and the practitioner will assign the participant to that intervention. The evaluator is blind to which intervention the participant accepts.

### Randomization

The computer-generated randomization is performed remotely by the Evidence-Based Medicine Center in Tianjin on the website of http://iwrs.tice.com.cn/.

### Blinding

The evaluator and the statistician are blinded; neither knows which intervention a participant accepts.

### Statistical methods

Categorical data will be analyzed with the McNemar chi-square test. We will use analysis of variance (ANOVA) to analyze continuous data. If the data trends over time and over time by treatment interactions, we will choose a repeated-measures analysis of variance (ANOVA). A *P* value less than 0.05 is regarded as statistically significant.

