## Methods/Design

### Trial design

This trial is designed as a four-armed parallel randomized controlled trial.

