## Participants

### Eligibility criteria

#### Inclusion criteria

The inclusion criteria include the following:Be diagnosed by histopathology as a tumor patient and accepts chemotherapy.The scoring of Karnofsky (KPS) must be more than 70.Patients of either gender, between 18 to 79 years old inclusive.Patients receiving chemotherapy as outpatients or inpatients.Patients receiving chemotherapy either for the first time or undergoing multiple cycles will be taken into the study only once.Receive cis-platinum (cis-platinum ≥75 mg/m2) or antharcycline combined chemotherapy (doxorubicin ≥40 mg/m2 or epirubicin ≥60 mg/m2)Life expectancy of at least 6 months.Willing to participate in the study and be randomly allocated into one of the four study groups.

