### Outcomes

#### Primary outcome

The primary outcomes are as follows:The frequency of nausea and vomitingTotal nausea and vomiting episodes per person over the 6-day study period will be recorded. The frequency of nausea and vomiting is the measurement with the most value for evaluation.The grading of nausea and vomitingThe Common Terminology Criteria for Adverse Events Version 4.0 [9] will be used to grade the nausea and vomiting.Rhodes Index of Nausea, Vomiting and RetchingThe Rhodes Index of Nausea, Vomiting and Retching [10], an eight-item validated scale, will be used to measure the nausea and vomiting experience, incidence and severity.

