### Secondary outcome measures

Secondary outcome measures include the following:The grading of constipation and diarrheaThe Common Terminology Criteria for Adverse Events Version 4.0 [9] will be used to evaluate the grading of constipation and diarrhea.ElectrogastrogramElectrogastrogram will be monitored to get the information of gastrointestinal motility.The assessment of quality of lifeThe Functional Assessment of Cancer Therapy - General (FACT-G) [11] will be applied to assess the quality of life.The assessment of anxiety and depressionThe Hospital Anxiety and Depression Scale [12] is a scale assessing anxiety with seven items and depression with a further seven items.Other adverse effects during the chemotherapyOther adverse effects during the chemotherapy, mainly including constipation and diarrhea, will be assessed by The Common Terminology Criteria for Adverse Events Version 4.0 [9].

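### McNemar, a paired test, is the only method named for categorical data, so the CTCAE nausea and vomiting grade (a primary outcome) has no valid comparison between the four independent arms

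*Protocol article*

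**What the plan says.** Three sentences in Statistical methods (protocol article) assign tests to data types.

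- Categorical data: "Categorical data will be analyzed with the McNemar chi-square test". No other test for such data is named anywhere in the article.
- Continuous data: "We will use analysis of variance (ANOVA) to analyze continuous data".
- Where there are trends over time or time-by-treatment interactions: "we will choose a repeated-measures analysis of variance (ANOVA").

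The design is described under Trial design: "This trial is designed as a four-armed parallel randomized controlled trial". The inclusion criteria say that patients "will be taken into the study only once". Under Allocation and sequence generation, "the computer will generate a random number and show which group the participant should be in".

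The categorical outcomes are CTCAE version 4.0 grades. Under Primary outcome, CTCAE "will be used to grade the nausea and vomiting", as the second of three listed items. Under Secondary outcome measures, the same criteria "will be used to evaluate the grading of constipation and diarrhea", and they are also used for other adverse effects of chemotherapy.

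**The concern.** McNemar's test asks whether the proportion with a condition differs between two readings on the same units. The question here is whether grades differ between patients allocated to different arms. The test named does not address that question, and it also needs a two-level variable, so the ordering of the grades would be lost.

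At stake is the randomised comparison for one of the three primary outcomes. An analyst who follows the sentence can only test change within an arm, for example day 0 against a later day. Day 0 comes before chemotherapy, so such a test mixes any treatment effect with the onset of chemotherapy toxicity. Setting the four within-arm verdicts side by side invites the claim that one acupoint works and another does not, when no test of that difference has been made.

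**Working it through.** The point turns on the structure of the test, so the main check sets the design against what the test requires. Two calculations support it.

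**1. What McNemar needs.** For paired binary readings, let *b* and *c* be the numbers of units that change in each direction. The statistic is (b − c)²/(b + c). It uses only the discordant pairs of a 2×2 paired table.

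**2. What the trial supplies.**

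| Requirement | Trial | Source in the protocol article |
|---|---|---|
| Paired units | Individually randomised patients, each in one arm; no matching or crossover described | Trial design; Inclusion criteria; Allocation and sequence generation |
| Two conditions | Four arms, so 4 × 3 / 2 = 6 pairs | Trial design |
| Binary reading | Ordinal CTCAE grade | Primary outcome; Secondary outcome measures |

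Between arms, *b* and *c* cannot be formed, so the statistic is undefined. It exists only within an arm, for two time points, after the grade is cut into two levels. Table 1 makes that possible, because grades are taken at day 0 and repeatedly afterwards.

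**3. The plan's own figure assumes independent arms.** Inputs from Sample size: means 12.5 and 11, SD 1.5 in each group, power 90%, type I error 5% (two-sided assumed), stated total 132. The standardised difference is (12.5 − 11)/1.5 = 1.

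- Normal approximation, n per arm = 2(z₁₋α/₂ + z₀.₉)²/1², α = 0.05: 22 per arm, 88 in four arms. Not reproduced.
- Same, α = 0.05/3: 28 per arm, 112 in total. Not reproduced.
- Same, α = 0.05/6: 31 per arm, 124 in total. Not reproduced.
- Unpaired t-test, α = 0.05/6: 32.5, rounded up to 33 per arm; 33 × 4 = 132. Reproduced.

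The article does not state this method. The match is, however, what an unpaired comparison with a Bonferroni allowance for all six pairs would give. The sample size thus appears to treat the arms as independent, while the categorical test treats readings as paired.

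**4. Why within-arm tests are no substitute.** This is an illustration only; the event rates are assumptions and do not come from the documents. Each of four arms has 33 patients with identical true rates, so there is no arm difference. Before and after readings are drawn independently, and an exact McNemar test at 0.05 is run in each arm (20,000 simulated trials).

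| Assumed rate before → after | Significant within an arm | Two given arms disagree | Four arms not all alike |
|---|---|---|---|
| 20% → 40% | 32% | 44% | 78% |
| 20% → 45% | 48% | 51% | 88% |
| 10% → 30% | 40% | 48% | 85% |

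As a check on the first row, two independent arms disagree with probability 2p(1 − p) = 2 × 0.323 × 0.677 = 0.437, close to the simulated 0.438.

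**The case against.** The article never says which outcomes count as categorical. CTCAE grades are numbers recorded daily, and the repeated-measures sentence is not restricted to particular outcomes. The authors might therefore analyse grades by repeated-measures ANOVA, which does compare arms. The sentence may also be a slip for the ordinary chi-square test, since no before/after analysis is announced and the sample size section aims at differences between pairs of groups. Finally, the damage is bounded. The article calls frequency the most valuable measure, sizes the trial on emesis number, and does not name the grade among the primary outcomes in the abstract.

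Part of this stands. Frequency and the Rhodes Index keep a between-arm analysis, and the main comparison survives. The before/after scenario is the only literal way to follow the sentence, but it is not a stated intention, and the simulated rates do not measure this trial.

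The rest does not rescue the sentence. A grade is categorical on its face, and nothing in the article moves it to ANOVA. If McNemar is a slip, the slip still governs a listed primary outcome. If it is meant for within-arm change, no between-arm test is stated for any categorical outcome, which is the same defect. An analysis plan not at hand may supply omitted detail, but it does not make a wrongly named test right.

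**Conclusion.** The concern holds: the sentence is wrong as written and must be corrected. No between-arm estimate or p-value for the CTCAE nausea and vomiting grade can come from the named test. The same applies to the constipation and diarrhea grades and other graded adverse effects. Needling reactions would be affected too if they are tested as present or absent; the article says only that they are recorded.

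The conclusion rests on two readings of the article: that CTCAE grades fall under categorical data, and that the arms are unpaired, as the design and allocation sections describe. It does not depend on the simulated rates. One of the three primary outcomes is affected, and the other two are not.

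**What to change.** Replace the McNemar sentence with methods for independent groups:

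- **CTCAE grades:** a proportional-odds (ordinal logistic) model with arm as a factor, adjusted for the day-0 grade. A Cochran–Mantel–Haenszel row-mean-score test is a simpler alternative; it need not be stratified, since no strata are described.
- **Grades repeated over days:** a cumulative-logit mixed model or GEE, or a single pre-stated summary of the daily grades analysed as above.
- **Binary items**, such as any vomiting or any needling reaction: logistic regression, or Pearson/Fisher tests.
- **Pairwise contrasts:** state the multiplicity rule. With four arms there are six pairs, and the sample size is consistent with 0.05/6.
- **McNemar:** at most a descriptive within-arm statistic.

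The team should choose one method and one time frame for the primary grade before analysis. The cost is a short change to Statistical methods. No extra data or patients are needed, and the sample size stands on this point because it rests on mean emesis number. The article reports that recruitment is still under way, so the correction can precede the analysis.

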	**Study Period**							
	**Enrollment**	**Allocation**	**Post-allocation**					**closeout**
Time point	-t1	0	t1	t2	t3	t4	t5	t6
Enrollment:								
Eligibility screen	×							
Informed consent	×							
Allocation		×						
Interventions:								
Control group								
Experimental group I			×	×	×	×		
Experimental group II			×	×	×	×		
Experimental group III			×	×	×	×		
Assessments:								
baseline variables	×	×						
The frequency of nausea and vomiting		×	×	×	×	×	×	×
The grading of nausea and vomiting		×	×	×	×	×	×	×
Rhodes Index of nausea, vomiting and retching		×	×	×	×	×	×	×
the grading of constipation and diarrhea		×	×	×	×	×		×
electrogastrogram		×					×	×
the assessment of quality of life		×					×	×
the assessment of anxiety and depression		×					×	×
other adverse effect during the chemotherapy							×	×
the adverse effects of acupuncture			×	×	×	×		

t1, the day before the chemotherapy; t1-t5, the first day to the fifth day of chemotherapy; t6, the 21st day of chemotherapy.

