### Sample size

Sample size calculation has been based on the result of a trial by *Shen J* [6] and the recommendation of acupuncture specialists in China. The mean value of emesis number in the Neiguan group is 12.5, the standard deviation is 1.5, and the mean value of emesis number in Neiguan plus Zhongwan group is 11, the standard deviation is 1.5. To detect a significant difference between any two groups with a power of 90% and type I error of 5%, the calculated number of patients is 132. Considering a 20% drop-out rate, the total sample size needs 160 patients.

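### Day-0 values of four continuous measures are collected, but the stated ANOVA methods name no baseline adjustment, which gives up precision that ANCOVA would recover at almost no cost

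*Protocol article*

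**What the plan says.** In the protocol article, Statistical methods, the rule for continuous outcomes is "We will use analysis of variance (ANOVA) to analyze continuous data". The next sentence adds a conditional alternative: "If the data trends over time and over time by treatment interactions, we will choose a repeated-measures analysis of variance (ANOVA"). No covariate, change score or other baseline term is named. The article does not say whether the response is the post-treatment value or a change, or whether day 0 is one of the time levels in the repeated-measures model.

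Table 1 marks these readings:

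- Rhodes Index, listed among the primary outcomes: time 0, t1 to t5, and t6 (day 21).
- FACT-G, which "will be applied to assess the quality of life" (Secondary outcome measures): time 0, t5 and t6.
- HADS, the row headed "the assessment of anxiety and depression": time 0, t5 and t6.
- Electrogastrogram: time 0, t5 and t6.

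A reading before chemotherapy is therefore available for all four.

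**The concern.** A baseline reading of the same scale is often the best available predictor of the later reading. The eligibility criteria admit first-cycle and multi-cycle patients, inpatients and outpatients, aged 18 to 79, so day-0 scores can plausibly differ between patients. An analysis that leaves day 0 out keeps that predictable variation in the error term, and any chance baseline difference between arms passes partly into the estimated contrast. With about 33 evaluable patients per arm, neither is negligible if baseline and outcome are well correlated.

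If day 0 enters as a level of time, the difficulty changes form: the arm main effect is then averaged over a reading that treatment cannot have affected. Because the choice between the two models depends on what the data show, the role of baseline is not settled in advance.

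**Working it through.** **The plan's own figure.** Sample size gives the inputs: "The mean value of emesis number in the Neiguan group is 12.5, the standard deviation is 1.5". For the arm treated at both points, the article assumes 11 with the same spread. The difference is 12.5 − 11 = 1.5, or 1.5/1.5 = 1.0 SD. The stated power is 90% and the type I error 5%. A two-sided t-test at 0.05 needs 23 per arm, or 4 × 23 = 92 in total, which is not the stated 132. Dividing 0.05 over the six pairs of arms gives 33 per arm, and 4 × 33 = 132 matches exactly. (The six-pair correction is inferred from this match; the article does not state it.) No baseline correlation enters, so the planned size neither relies on adjustment nor changes with it. With 160 randomised equally and 20% lost, 160 × 0.8 / 4 = 32 per arm remain.

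**Precision with and without baseline.** Let r be the correlation between the day-0 value and the outcome. The documents do not give it; 0.3 to 0.7 is assumed. With equal variances at both times, the variance of an arm contrast relative to ANOVA of the post-treatment value is:

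- change score: 2(1 − r)
- ANCOVA: 1 − r²

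| r | Change score | ANCOVA | Variance cut by ANCOVA | Interval-width factor √(1 − r²) | Width cut |
|---|---|---|---|---|---|
| 0 | 2.00 | 1.00 | 0% | 1.000 | 0% |
| 0.1 | 1.80 | 0.99 | 1% | 0.995 | under 1% |
| 0.3 | 1.40 | 0.91 | 9% | 0.954 | 5% |
| 0.5 | 1.00 | 0.75 | 25% | 0.866 | 13% |
| 0.7 | 0.60 | 0.51 | 49% | 0.714 | 29% |

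The change score is never more precise than ANCOVA, since 2(1 − r) − (1 − r²) = (1 − r)² ≥ 0. Below r = 0.5 it is less precise than ignoring baseline.

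In terms of numbers, 132 patients analysed with adjustment carry the information of 132/(1 − r²) unadjusted patients: 145, 176 and 259 at r = 0.3, 0.5 and 0.7.

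**Illustrative power.** At 32 per arm, two-sided 0.05 and an assumed effect of 0.5 SD, the unadjusted standard error is √(2/32) = 0.25 SD and power is 51.6%. With adjustment it is 55.4%, 63.7% and 80.0% at r = 0.3, 0.5 and 0.7.

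**Chance imbalance.** A baseline difference of 0.25 SD between two arms shifts the unadjusted contrast by 0.25r SD: 0.075, 0.125 and 0.175 SD at the same three values of r.

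**Day 0 as a level of time.** Suppose the effect is δ at each of k post-baseline readings and zero at day 0. The arm main effect averages k + 1 levels and estimates kδ/(k + 1).

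- Rhodes Index (0, t1 to t6): k = 6, giving 6/7 of δ, a 14% shrinkage.
- FACT-G, HADS and electrogastrogram (0, t5, t6): k = 2, giving 2/3 of δ, a 33% shrinkage.

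These factors describe the size of the estimate; they are not power figures.

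**The case against.** The strongest reply is that the article is a condensed account, and that covariates and the exact response are commonly left to a fuller document. Nothing in Statistical methods says that day-0 values will be set aside. A reader might infer that the arms will be compared without them, but the text does not establish this: an ANOVA of change scores is not excluded, and the repeated-measures model could include day 0, in which case its time-by-treatment term tests whether change from baseline differs between arms. That stands, and the point is therefore limited to what the stated methods name. It does not remove the point, because the article does choose a method, and the readings it permits are no better: change scores are never more precise than ANCOVA, and day 0 as a level of time dilutes the arm main effect.

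A reader might also infer that the planned analysis is biased or invalid. It is not. Allocation is randomised, so unadjusted ANOVA is unbiased on average, and chance imbalance is already allowed for in the type I error rate.

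The size is also open to challenge. No figure in the article supports any value of r. The Rhodes Index is the only primary outcome among the four, and its day-0 reading precedes chemotherapy. Several other causes of nausea and vomiting are excluded, so scores may sit near the floor and adjustment may gain little. A useful gain is more plausible for FACT-G and HADS, which are secondary; that is a judgement. Nor would adjustment remove most of the variance: over the assumed range it always removes less than half.

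**Conclusion.** The point holds as a matter of efficiency and specification. Four measures have a scheduled day-0 value, and the methods fixed for continuous data name no baseline adjustment. Against an ANOVA of post-treatment values, ANCOVA would reduce residual variance by 9% to 49% and interval width by 5% to 29% for an assumed r of 0.3 to 0.7, and by close to nothing if r is near 0. If day 0 is entered as a level of time, a constant effect appears in the arm main effect at 6/7 of its size for the Rhodes Index and 2/3 for the other three measures, although the interaction term still uses baseline. These results assume equal variances over time and, for the dilution, an effect constant over the post-baseline readings. The sample size is unaffected. The change is worth making because it costs so little, not because the stated analysis is wrong.

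**What to change.** State in Statistical methods, before any outcome data are examined by arm, that:

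- the Rhodes Index, FACT-G, HADS and electrogastrogram parameters are compared between arms by analysis of covariance, with the day-0 value of the same measure as covariate;
- where several post-baseline readings are modelled together, the response is the post-baseline values only, and day 0 enters as a covariate and not as a level of time;
- this handling of baseline does not depend on the trends or interactions observed.

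The cost is one or two sentences and one degree of freedom per model. With four arms of 32, the residual degrees of freedom in a single-time-point model go from 128 − 4 = 124 to 123. No new data or visits are needed, and the sample size stays as it is.

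### The choice between ANOVA and repeated-measures ANOVA is tied to the observed time trend and treatment-by-time interaction, and neither effect is named as the primary treatment test

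*Protocol article*

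**What the plan says.** Under Statistical methods, the default for continuous outcomes is: "We will use analysis of variance (ANOVA) to analyze continuous data". The next sentence gives the condition for changing method: "If the data trends over time and over time by treatment interactions, we will choose a repeated-measures analysis of variance (ANOVA"). The significance rule is that a P "value less than 0.05 is regarded as statistically significant". The section does not say whether the arm main effect, the interaction or either of them answers the treatment question.

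Three other places bear on this:

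- Primary outcome (under Outcomes) gives most weight to the number of nausea and vomiting episodes per person, totalled over six days. Table 1 schedules this outcome on day 0, on days 1 to 5 and again on day 21.
- Sample size plans on means and standard deviations of the emesis count, then allows for attrition: "Considering a 20% drop-out rate, the total sample size needs 160 patients".
- Blinding states that the evaluator and the statistician do not know the allocation.

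**The concern.** When the results choose the method, the reported P value no longer comes from one procedure fixed in advance. The trigger makes this worse here. A treatment-by-time interaction is a difference between arms in how symptoms develop, so a chance interaction both changes the analysis and offers a second result that could be reported as an effect of electroacupuncture.

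The two methods may also not use the same patients. Classical repeated-measures ANOVA works on patients with a value on every day. A one-way ANOVA on a patient's total or mean can take in whoever has that summary. With a fifth of patients expected to drop out, the switch could change who is analysed as well as how. If leaving is related to symptoms, the analysis of completers could be biased.

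**Working it through.** **Planning figures.** "The mean value of emesis number in the Neiguan group is 12.5, the standard deviation is 1.5"; "the mean value of emesis number in Neiguan plus Zhongwan group is 11, the standard deviation is 1.5". The difference is 12.5 − 11 = 1.5, which is 1 SD. The article asks for 90% power and 5% type I error for any two of four groups, which gives six pairs. A two-sample t test at 0.05/6 needs 33 per arm, and 4 × 33 = 132, matching "the calculated number of patients is 132". For drop-out, 33 × 1.2 = 39.6, or 40 per arm, giving 160. Equal allocation and two-sided tests are assumed. The match does not prove that this was the method used, but 33 per arm is a suitable size for the checks.

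**Step 1: is the arm test the same under both methods?** With N patients, T days and complete data, the group sum of squares in repeated-measures ANOVA is T times that of the patient means. The between-patient error sum of squares is scaled by the same T, so F for arm equals the one-way F on patient means or totals. In the check runs the two P values agreed (for example 0.8227 and 0.8227). The switch alone therefore does not inflate the arm test when data are complete.

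**Step 2: what if the interaction may also count?** For two independent tests at 5%, 1 − 0.95² = 0.0975. The stated rule was also simulated with no treatment effect: 4 × 33 patients, six time points, 5,000 runs per scenario. The switch occurs when time and interaction both have P < 0.05. Success is arm P < 0.05, or a switch with the interaction read as an effect.

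| Assumed data | Arm main effect only | Arm or interaction, uncorrected | Arm or interaction, Greenhouse-Geisser |
|---|---|---|---|
| Normal, equal correlation 0.5 | 0.046 | 0.104 | 0.100 |
| Normal, AR(1) 0.7 | 0.048 | 0.133 | 0.097 |
| Skewed counts (skewness of totals about 3.1) | 0.043 | 0.094 | 0.071 |

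The assumed daily profile rises and falls, so the time effect was significant in every run and the interaction alone drove the switch. Simulation error is about √(0.1 × 0.9/5000) = 0.004.

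**Step 3: what does drop-out do?** The expected loss is 0.20 × 160 = 32 patients, leaving 128, or 32 per arm. Power for a 1-SD difference at 0.05/6 (two-sample t) is 0.894 with 32 per arm and 0.905 with 33, so little power is lost.

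The identity in step 1 does not survive missing days. Null trials were simulated with 4 × 40 patients, six time points, correlation 0.5 and 20% random drop-out, comparing an ANOVA of available-day means with an analysis of completers. Each test kept its level (0.048 and 0.050). They disagreed on significance in 5.2% of trials, and at least one was below 0.05 in 7.5%.

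**The case against.** The strongest reply is that the sentence is badly phrased and means only that repeated-measures ANOVA will be used for questions about change over time. On that reading the question, not the result, selects the method, and the data dependence disappears. That may be what was intended, but it is not what the sentence says. Silence about the primary contrast could by itself be filled by an analysis plan that is not shown. The point rests on the conditional rule that is printed.

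Four stronger readings are tempting, and the article does not support them:

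- *Error rates are uncontrolled in general.* They are not. The arm main effect kept its level in every scenario, and the rise to about 10% needs the interaction to count as success, which the article neither says nor rules out.
- *The choice is made on unblinded data.* Blinding states that the statistician is blinded. Coded groups can still show an interaction, so blinding does not remove the dependence, but unblinding is not the problem.
- *ANOVA is invalid because the counts are skewed with many zeros.* The article gives no sign of this. Its planning SDs are equal at 1.5 around means of 12.5 and 11, whereas a Poisson count with mean 12.5 would have an SD of √12.5 = 3.5. Strong simulated skewness did not inflate the arm test either.
- *The plan deletes incomplete patients.* No such rule is stated. Needing complete rows is a property of classical repeated-measures ANOVA. The article does not say when patients leave or what data they provide, and detailed missing-data rules may lie in a fuller document.

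**Conclusion.** The point holds in a limited form. The stated rule lets the observed trend and interaction select the method and leaves the primary treatment test open. If only the arm main effect counts, the error rate is about 5% and no harm follows with complete data. If the interaction may also count, the false-positive chance is about 7 to 13%, depending on the assumed correlation, distribution and sphericity correction. With drop-out, the two methods could rest on different patients. The cost in power is about one percentage point; the larger risks are bias if leaving is related to symptoms, and unused partial data.

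These sizes depend on equal allocation, six daily time points, and assumed correlations, time profile and drop-out pattern, none of which the article gives apart from the 20% rate and the daily schedule from day 0 to day 5.

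**What to change.** Replace the conditional sentence with one model fixed in advance, whatever the time trend:

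- **Primary contrast:** the between-arm difference over the post-baseline days, stating which arms it compares. Arm by day is secondary and is not a second route to success.
- **Data and covariate:** all randomised patients and every observed day, with the day-0 value as covariate. State whether day 21 is left out of the primary contrast.
- **Rhodes Index:** a likelihood-based mixed model for repeated measures.
- **Nausea and vomiting episode counts:** a mixed model, or GEE with robust standard errors. Report the effect as a mean difference, the scale of the sample size calculation, or as a rate ratio.

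A negative binomial form need not be prescribed. The planning figures imply a variance (1.5² = 2.25) below the mean (12.5), which that distribution cannot represent.

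The cost is a few sentences under Statistical methods and slightly more analysis work, with no extra patients or visits. If a rate ratio is chosen, the effect scale will differ from the one used for the sample size, and the plan should say so. If the six-day total includes day 0, using day 0 as covariate moves it out of the outcome. On the mean-difference scale with complete data, the adjusted arm contrast is the same either way.
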